## PROTOCOL OUTLINE

### TRIAL TITLE

**Nordics and Switzerland, Prospective Multi-centre Non-Interventional ObServational Trial to Assess the Pattern of Use of REKOVELLE® in Women Undergoing In Vitro Fertilisation (IVF) or Intracytoplasmic Sperm Injection (ICSI) Procedures in Routine Clinical Practice (NORSOS)**

### PLANNED TRIAL PERIOD

The total duration of the trial will be approximately 24 months (from Ethics Submission to LSLV).

| Trial Milestone                               | Estimated Date |
|------------------------------------------------------|-----------------------|
| Ethics submission                                    | Q2 2022               |
| Site Initiation visits                               | Q3 2022               |
| Start of data collection (first subject first visit) | Q3 2022               |
| Last subject inclusion                               | Q4 2023               |
| End of data collection (last subject last visit)     | Q1 2024               |
| Data base lock                                       | Q1 2024               |
| Final Trial Report                                   | Q2 2024               |

### OBJECTIVES

#### **Primary objective**

To observe the usage patterns of REKOVELLE®, in women naïve to in vitro fertilisation (IVF) and intracytoplasmic sperm injection (ICSI), undergoing their first COS treatment cycle with REKOVELLE® in routine clinical practice.

#### **Secondary objectives**

- To observe the ovarian stimulation and embryo development outcomes of REKOVELLE® in routine clinical practice after the 1st treatment cycle.
- To observe the safety profile of REKOVELLE® in routine clinical practice after the 1st treatment cycle.

- To observe the subject satisfaction of overall REKOVELLE® treatment and REKOVELLE® pre-filled pen usage in naïve subjects in routine clinical practice after 1st treatment cycle.

## **ENDPOINTS**

### **Primary endpoint**

Treatment patterns in first cycle with REKOVELLE®:

- Use of the algorithm-based individualised dosing regimen (daily dose of REKOVELLE® administered), number of days of treatment, dose changes; use of the Algorithm dosing Application; use of GnRH protocol, type of GnRH protocol, triggering of follicle maturation; luteal phase support.

### **Secondary endpoints**

Ovarian stimulation and embryo development outcomes of REKOVELLE® in routine clinical practice:

- Rate of ongoing pregnancy ( $\geq 1$  intrauterine viable fetus 10-11 weeks after embryo transfer) in the fresh cycle
- Rate of ongoing pregnancy ( $\geq 1$  intrauterine viable fetus 10-11 weeks after embryo transfer) following the fresh cycle, including also the first frozen embryo transfer
- Number of oocytes retrieved
- Number of oocytes/embryos/blastocysts frozen
- Number of embryos/blastocysts transferred
- Quality of fresh embryos or blastocysts transferred (excellent, good, fair, other)
- Positive signs of pregnancy (hCG test or urine pregnancy test) and clinical pregnancy (at least one gestational sac 5-6 weeks after transfer)
- Pregnancy loss in women with embryo/blastocyst transfer (biochemical pregnancy, spontaneous/elective abortion, ectopic pregnancy, vanishing twin)
- Cycle cancellation before or after oocyte pick-up and reason for cycle cancellation

Safety profile of REKOVELLE® in routine clinical practice:

- Adverse drug reactions (ADRs)
- OHSS (including mild/moderate/severe)
- Preventive interventions for early ovarian hyperstimulation syndrome (OHSS): Triggering of final follicular maturation with GnRH agonist, cancellation of fresh embryo/blastocyst transfer

Subject satisfaction with REKOVELLE® in routine clinical practice:

- Assessment of overall subject experience and convenience with REKOVELLE® by the Subject Questionnaire (assessed by the subject)

## METHODOLOGY

This is a European trial including Nordic Countries (Sweden, Denmark, Norway) and Switzerland. A Prospective, multi-centre, post-authorisation, non-interventional observational cohort trial conducted under routine clinical practice in fertility clinics to collect information from 200 naïve women treated with REKOVELLE® and undergoing IVF or ICSI procedures.

As the trial is non-interventional, the decision to treat subjects with REKOVELLE® will be independent from the decision to enrol the subject into the trial. Subjects will be enrolled only after the treatment decision has been made and no aspect of this trial will interfere with or influence the routine medical procedures and/or medications received. No trial medications will be provided.

In each site, during the enrolment period, consecutive women who are prescribed REKOVELLE® for IVF/ICSI cycle according to the approved label, will be invited to participate in the trial. The trial enrolment will be monitored, and the enrolment will be locked once 200 women have initiated treatment. Each woman will contribute only for one stimulation cycle over the observation period.

During the observation period, the investigators will collect data for 1 stimulation cycle with REKOVELLE® or until early withdrawal. Data about cycles using frozen embryos/blastocysts will be collected only for the first transfer cycle if they are performed within 3 months after the cycle stimulated with REKOVELLE® within the observation period.

Women with embryo/blastocyst transfer will be followed until ongoing pregnancy (approximately 10-11 weeks after the first fresh or frozen transfer), or no pregnancy is confirmed or early pregnancy loss, or trial withdrawal. Ultrasound results must be obtained if not performed at the participating site.

Baseline, COS treatment and follow-up assessments will be performed by the investigators during routine local clinical care visits.

Subject questionnaire will be completed by the subjects at the clinic after cycle cancellation, trial withdrawal or before the oocyte retrieval.

## NUMBER OF SUBJECTS

There will be 200 subjects initiated with REKOVELLE® treatment and enrolled (signs Informed Consent Form (ICF) to participate in the study)

## CRITERIA FOR INCLUSION / EXCLUSION

Subjects who meet **all** of the following inclusion criteria and who do not meet **any** of the following exclusion criteria are eligible for participation.

### Inclusion criteria

- Females aged 18 years or older at enrolment
- Who have never been treated with (naïve) *in vitro* fertilisation (IVF) or intracytoplasmic sperm injection (ICSI) treatment using fresh or frozen ejaculated sperm from male partner or sperm donor
- Who are prescribed REKOVELLE® for the first time, using the dosing algorithm-based on AMH test result and body weight to define the 1st cycle dose regimen with REKOVELLE® according to the approved label
- Who have been informed verbally and in writing about this trial content, signed the inform consent and who do not object to their data being electronically processed

#### **Exclusion criteria**

- Currently participating in an interventional clinical trial in which any treatment or follow-up is mandated
- Women with a contraindication for prescription of REKOVELLE® treatment
  - Hypersensitivity to the active substance or to any of the excipients
  - Tumours of the hypothalamus or pituitary gland
  - Ovarian enlargement or ovarian cyst not due to polycystic ovarian syndrome
  - Gynaecological haemorrhages of unknown aetiology
  - Ovarian, uterine, or mammary carcinoma
  - Primary ovarian failure
  - Malformations of sexual organs incompatible with pregnancy
  - Fibroid tumours of the uterus incompatible with pregnancy
  - Pregnancy and breast feeding
- Women who undergo ovarian stimulation for fertility preservation
- Women placed under judicial protection, guardianship, or supervision
- Women who are considered as vulnerable population

#### **MEDICINAL PRODUCT**

REKOVELLE® (follitropin delta), solution for injection - delivered in a pre-filled injection pen.

Indicated dose according to approved label. Subjects must be treated in the usual manner in accordance with the terms of the marketing authorisation.

The REKOVELLE® dose should be based on a recent determination of body weight and AMH (i.e., within the last 12 months) measured by one of the alternative assays for dose selection; ELECSYS AMH Plus Immunoassay from Roche, or ACCESS AMH Advanced from Beckman Coulter or LUMIPULSE G AMH from Fujirebio.

#### **DURATION OF PARTICIPATION**

Women will be enrolled in each site over the enrolment period and will contribute for one stimulation cycle of REKOVELLE® in routine clinical practice, over the observation period. Women with embryo/blastocyst transfer will be followed until the ongoing pregnancy (approximately 10-11 weeks after the first fresh or frozen transfer).

First transfer cycles with frozen embryo (or blastocyst) will be followed if they are performed within 3 months after the stimulation cycle with REKOVELLE® within the enrolment period.

Non-pregnant women will be followed for 1 stimulation cycle with REKOVELLE® or until early withdrawal.

## **STATISTICAL METHODS**

### **Statistical analysis**

This is a descriptive trial. There are no hypotheses to be tested and no inferential statistics will be applied. All descriptions of data will be based on all subjects enrolled in the trial who meet the inclusion/exclusion criteria and who receive at least one dose of REKOVELLE®. Therefore, pregnancy rates will be calculated for all subjects starting stimulation with REKOVELLE®, and mean number of oocytes, embryos, blastocysts etc. will be the mean for all subjects starting stimulation with REKOVELLE®.

Missing data for pregnancy outcomes will be regarded as “no pregnancy”. Missing data for number of oocytes, number of embryos, number of blastocysts, and similar endpoints will be regarded as zero.

The primary endpoint, real-life treatment patterns in first cycle with REKOVELLE® will be extensively described.

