#### **8.2.1 General Considerations**

All data will be summarized using descriptive statistics:

- Continuous variables will be described (distribution) by their mean, standard deviation, median, quartiles 1 and 3, extreme values (minimum and maximum) and the number of missing data.
- Categorical variables will be described (counts) by the number and percentage of each response and the number of missing data.

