### **8.3.4 Analysis of the Secondary Endpoints**

Assessment of the Ovarian stimulation and embryo development outcomes of REKOVELLE®: the following descriptive analyses will be performed based on the Analysis Population:

- Rate of ongoing pregnancy ( $\geq 1$  intrauterine viable fetus 10-11 weeks after embryo transfer) in the fresh cycle will be calculated

- Rate of ongoing pregnancy ( $\geq 1$  intrauterine viable fetus 10-11 weeks after embryo transfer) following the fresh cycle, including also the first frozen embryo transfer, will be calculated
- The distribution of the number of oocytes retrieved will be described
- The distribution of the number of oocytes/embryos/blastocysts frozen will be described
- The type of embryos/blastocysts transferred (fresh or frozen), the number and quality of embryos/blastocysts transferred (excellent, good, fair, other), and the day of embryo/blastocyst transfer will be described
- The Positive signs of pregnancy (hCG test or urine pregnancy test) and clinical pregnancy (at least one gestational sac 5-6 weeks after transfer) will be calculated
- The rate of pregnancy loss (biochemical pregnancy, spontaneous / elective abortion, ectopic pregnancy, vanishing twin) will be calculated
- The rate of cycles cancelled before or after oocyte pick-up will be calculated and the reason for cancellation will be described

Assessment of REKOVELLE® safety: the following descriptive analyses will be performed on the Safety Population:

- Description and rates of ADRs and SADR to REKOVELLE®: all events will be coded by SOC (System Organ Class) and PT (Preferred Term) using MedDRA lowest level term (LLT)

The following descriptions will be made:

- Number and proportion of subjects experiencing at least one ADR/SADR, and corresponding number of events
- Number and proportion of subjects experiencing each ADR/SADR, and corresponding number of events
- ADR/SADR severity and outcomes (fatal, temporary / permanent discontinuations)
- All fatal AEs regardless of causality
- The rate of mild, moderate, severe early and late OHSS will be calculated. The time to OHSS occurrence and the OHSS duration will be described. The duration of hospitalisation, the medical and surgical interventions and the OHSS outcomes will be described
- The rate of preventive interventions for early OHSS will be calculated
- The drop-out rate will be calculated and the reasons for drop-out as reported by the women will be described

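### Read literally, the mean number of embryos transferred is taken over all women starting stimulation, which mixes the chance of reaching a transfer with the number transferred

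*Protocol*

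**What the plan says.** The Protocol Outline, under Statistical analysis, fixes one denominator for everything: "All descriptions of data will be based on all subjects enrolled in the trial who meet the inclusion/exclusion criteria and who receive at least one" (the sentence closes by naming a dose of the product). It then draws the consequence for counts, namely that the "mean number of oocytes, embryos, blastocysts etc. will be the mean for all subjects starting stimulation with REKOVELLE", and adds an imputation rule: "Missing data for number of oocytes, number of embryos, number of blastocysts, and similar endpoints will be regarded as zero".

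The secondary endpoints, in the outline and in section 3.2, include "Number of embryos/blastocysts transferred", with no restriction to women who had a transfer. Pregnancy loss, in the same list, is restricted to women with a transfer.

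Section 8.3.4 introduces the stimulation and embryo outcomes with the statement that "the following descriptive analyses will be performed based on the Analysis Population". Section 8.2.2 defines that population as eligible, enrolled women with at least one dose. The relevant bullet says that the type (fresh or frozen) and "the number and quality of embryos/blastocysts transferred (excellent, good, fair, other), and the day of embryo/blastocyst transfer will be described". Section 8.3.4 ends by planning descriptions of the secondary endpoints by age, AMH level, ovarian response and country.

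Section 8.2.1 sets the summary statistics: "Continuous variables will be described (distribution) by their mean, standard deviation, median, quartiles 1 and 3", then the minimum, the maximum and the number of missing values. Categorical variables are given as number and percentage.

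**The concern.** For oocytes retrieved, a mean over all starters is a sensible measure of yield, and a woman whose cycle is cancelled before pick-up properly contributes zero. The number of embryos transferred is a different kind of quantity. It describes what was done at a transfer, and its natural unit is the transfer.

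The protocol itself foresees women without a transfer. Section 6.2.3 lists cancellation before pick-up, transfer cancellation after pick-up and freeze-all, and section 4.1 collects only the first frozen transfer, within 3 months. Under the stated rule these women enter as zeros, whether the zero is treated as a true value or as the replacement for a blank.

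What is at stake is how the result is read. A low mean may come from few embryos per transfer or from few women reaching a transfer. The planned subgroups make this more than theoretical. Poor and excessive ovarian response are both listed reasons for cancellation before pick-up, and cancelling the fresh transfer is a listed preventive measure for OHSS. Women without a fresh transfer may therefore cluster in particular response or AMH groups. A lower subgroup mean could then look like more restrictive transfer practice when it reflects cancellation.

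**Working it through.** The protocol states no figure for this endpoint, and its 200 subjects have no inferential basis, so there is nothing to reproduce. The check is an identity with assumed rates.

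**Inputs**
- N = 200 starters (Protocol Outline, Number of Subjects).
- P, the proportion of starters reaching the transfer in question: not in the protocol, assumed.
- d, the proportion of transfers that are double, the rest being single: not in the protocol, assumed.

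**Formula.** Mean per transfer = 1 + d. With zeros for women without a transfer, mean per starter = P × (1 + d).

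**Step 1: different practice, same mean.**
- P = 0.8, d = 0: 160 transfers, 160 embryos. Per starter 160/200 = 0.80; per transfer 160/160 = 1.0.
- P = 0.5, d = 0.6: 100 transfers, 160 embryos. Per starter 160/200 = 0.80; per transfer 160/100 = 1.6.

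**Step 2: same practice, different mean.** Hold d = 0.2, so that the mean per transfer is 1.20 throughout.
- P = 0.80: 0.80 × 1.2 = 0.96
- P = 0.65: 0.65 × 1.2 = 0.78
- P = 0.50: 0.50 × 1.2 = 0.60

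Two subgroups with P = 0.80 and P = 0.50 would show 0.96 and 0.60 with identical practice at transfer.

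**Step 3: when the mean falls below one.** This needs P < 1/(1 + d): P below 0.833 for d = 0.2, below 0.667 for d = 0.5 and below 0.500 for d = 1.0.

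**Step 4: unrecorded counts.** With P = 0.6 and d = 0.5 the mean is 0.90. If 5% of women with a transfer lack a recorded count and are set to zero, it becomes 0.6 × 0.95 × 1.5 = 0.855.

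**Step 5: what the other statistics in section 8.2.1 show.** For the pair in step 1, variance = mean square minus squared mean.
- P = 0.8, d = 0: 0.80 − 0.64 = 0.16, SD 0.40, maximum 1.
- P = 0.5, d = 0.6: 20% of starters have 1 embryo and 30% have 2, so the mean square is 0.2 + 4 × 0.3 = 1.40. Variance is 1.40 − 0.64 = 0.76, SD 0.87, maximum 2.

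The two are distinguishable. For a count limited to 0, 1 or 2 the mix can even be solved: P(double) = (SD² + mean² − mean)/2 and P(transfer) = mean − P(double).
- Second line of the pair: (0.76 + 0.64 − 0.80)/2 = 0.30 and 0.80 − 0.30 = 0.50, so the double share is 0.30/0.50 = 60%.
- Middle case of step 2: mean 0.78, variance 0.4316. (0.4316 + 0.6084 − 0.78)/2 = 0.13 and 0.78 − 0.13 = 0.65, so the double share is 20%.

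This works only if fresh and frozen transfers are tabulated separately. If they were added up per woman, a 2 could be one double transfer or two single ones.

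**The case against.** The strongest reply has four parts.

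- **The rule may not be meant for this endpoint.** The outline's sentences name oocytes, embryos and blastocysts, which fits yield, and never mention transfer. The bullet in section 8.3.4 places number beside quality and day, which exist only where a transfer took place, so it reads naturally as a description of transfers. This has weight as to intent. As written, though, the sentence on all descriptions, the open-ended list of counts, the reference to similar endpoints and the Analysis Population in section 8.3.4 all bring the endpoint in, and nothing takes it out. The bullet is left with items that cannot share one denominator.
- **The information is not lost.** A reader might infer that the output cannot separate single-transfer from double-transfer practice, or that the double share cannot be recovered. The documents do not support that. Section 8.2.1 also requires the SD, quartiles, minimum and maximum, and step 5 shows that these separate the examples. Nor does any text say that fresh and frozen counts are added per woman; section 6.2.3 collects them separately. What remains is that a listed endpoint should not need back-calculation.
- **There is no bias.** A reader might call the all-starters mean 20%, 35% or 50% too low in the cases of step 2. That treats the per-transfer mean as the true target. The two are different quantities, and a woman without a transfer did have zero embryos transferred.
- **The layout belongs to the statistical analysis plan.** A count of 0, 1 or 2 could be tabulated as categories, and the plan, which is not shown, may do so. Cancellation rates are reported in any case. But the denominator is not left open: the protocol states one, and a summary restricted to women with a transfer would depart from it.

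**Conclusion.** The point holds as a minor one. As written, the all-starters rule and the zero rule cover the number of embryos or blastocysts transferred. The resulting mean is a product of two things that readers will want apart: how often a transfer was reached, and how many embryos were then transferred. Differences between the ovarian response, AMH or country subgroups may reflect the first rather than the second.

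The sizes are illustrative only. Identical means of 0.80 can stand for 1.0 or 1.6 per transfer, and identical practice of 1.20 per transfer can show as anything from 0.96 to 0.60 when 20% to 50% of starters have no transfer. All these rates are assumptions. That the mean will fall below one should not be inferred: with half of transfers double, more than a third of starters would have to be without a transfer.

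The endpoint is secondary and descriptive, no inference depends on it, and the SD and range partly reveal the mix. The all-starters denominator remains sound for pregnancy rates and oocyte yield.

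**What to change.** Amend the statistical analysis paragraph of the Protocol Outline and the transfer bullet of section 8.3.4:

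- Keep the all-starters mean for oocytes retrieved and for oocytes, embryos and blastocysts frozen.
- Describe number, quality and day of embryos or blastocysts transferred among women with that transfer, separately for the fresh and the first frozen transfer, with number given as n (%) with 1, 2 or more.
- Beside it, give the share of all starters who reached each transfer, so that the per-starter view is kept.
- State that the zero rule does not apply to women without a transfer in this summary.

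This follows the protocol's own practice for pregnancy loss, which is already confined to women with a transfer, and section 6.2.3 already collects the fresh and frozen data separately. The cost is one sentence, one extra table and a second denominator that must be clearly labelled. No new data are needed.

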### 5.3 Trial Withdrawal/Treatment Discontinuation Criteria

Participation in this trial is voluntary and women are free to withdraw from the trial at any time and for any reason without prejudice to their drug prescriptions or therapeutic management. Missing routine care visits at one or more time points or missing questionnaires will not be considered as criteria for Subject withdrawal.

If a woman withdraws from the trial, regardless of cause, the date and the reason for trial withdrawal will be documented in the e-CRF, if this information is available. Subjects who withdraw from the trial will be informed that data collected up to that point will be used in the trial analyses but that after withdrawal no further data will be collected for them.

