### 6.2.3 Follow-up

No visits are mandated or prescheduled as part of the trial. Follow-up information will be collected by the physicians at one single visit scheduled as a part of routine care or may be collected via a telephone interview if a visit does not occur.

The following data will be collected for the 1st cycle with REKOVELLE®:

- Ultrasound results since last visit, as available
- Antral follicle count, as available
- Luteal phase support
- OHSS (including mild/moderate/severe)
- Preventive measures for OHSS:
  - Triggering of final follicular maturation with GnRH agonist and cancellation of fresh embryo/blastocyst transfer
- Oocytes retrieval: number of oocytes retrieved, number of metaphase II (MII) oocytes
- Number of frozen oocytes/embryos/blastocysts
- Freeze all strategy: reasons for freeze all strategy as alternative to fresh embryo transfer
- Fresh embryo/blastocyst transfer: day of embryo/blastocyst transfer, number and quality of embryos/blastocysts transferred
- Frozen embryo/blastocyst transfer (FET): endometrial preparation protocol, date of FET, number and quality of embryos/blastocysts transferred
- Pregnancy outcome: positive hCG, clinical pregnancy, vital pregnancy, ongoing pregnancy
- Pregnancy loss: biochemical pregnancy, spontaneous abortion, elective abortion, ectopic pregnancy, vanishing twin
- Cycle cancelled before oocyte pick-up, Transfer Cancellation, and reason for cycle cancellation:
  - Cancellation before oocyte pick-up (poor ovarian response, excessive ovarian response, any illness which prevents oocyte collection procedure, subject not taking hCG injection at the correct time, subject choice, other)
  - Transfer Cancellation after oocyte pick-up (no oocytes collected, no oocytes fertilised, abnormal fertilisation, abnormal embryo development, no embryo development, OHSS, subject choice, other)
- ADRs serious and non-serious, related / non-related fatal events

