## **8 STATISTICAL METHODS**

### **8.1 Sample Size**

The sample size was planned to ensure that the trial obtains meaningful estimates for the description of REKOVELLE® patterns of use, ovarian stimulation and embryo development outcomes, and safety and subject satisfaction at the 1st cycle with REKOVELLE®.

This trial will be conducted in Nordic Countries (Sweden, Denmark, Norway) and Switzerland with the activation of 15 sites, known to follow-up women undergoing ART and to regularly prescribe REKOVELLE®. Each site will enrol maximum 15 subjects during the predefined inclusion period, until the total 200 subjects initiated with REKOVELLE® treatment enrolment target achieved in a competitive manner.

As the statistical analyses will be purely descriptive, the sample size is not based on any inferential statistical considerations.

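### Unknown oocyte, embryo and blastocyst counts are set to zero along with documented non-events, which lowers the secondary count means

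*Protocol*

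**What the plan says.** The rule stands in the Protocol Outline, Statistical analysis: "Missing data for number of oocytes, number of embryos, number of blastocysts, and similar endpoints will be regarded as zero". The same paragraphs set the denominator, so that the "mean number of oocytes, embryos, blastocysts etc. will be the mean for all subjects starting stimulation with REKOVELLE". A companion sentence, beginning "Missing data for pregnancy outcomes will be regarded as", assigns missing pregnancy outcomes to the not-pregnant category.

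Four other places bear on the point:

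- Section 5.3 says of women who withdraw that "after withdrawal no further data will be collected for them".
- Section 6.2.3 collects cancellation before pick-up and cancellation of transfer, each with a reason. Failure to collect any oocytes is one of the listed reasons.
- Section 8.2.1 lists, among the summaries for continuous variables, "extreme values (minimum and maximum) and the number of missing data". Section 8 does not repeat the zero rule.
- Section 8.3.4 ends by describing primary and secondary endpoints in subgroups, one of which is ovarian response. It gives no definition or cut-offs for that subgroup.

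**The concern.** Two different situations receive the same value. In the first, the event did not happen: the cycle was cancelled before pick-up, no oocyte was found, nothing was frozen, or no transfer was done. Over all started cycles, zero is then the true count. In the second, the event may well have happened but the number is not in the database. Zero is then not an observation, and for most such women it is probably wrong.

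The e-CRF already separates the two, so the first situation needs no imputation. What the rule adds falls on the second. A woman who leaves the study during stimulation and has oocytes collected the following week in routine care is analysed as having none.

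At stake are the means and spreads of the count endpoints. If ovarian response is defined by oocyte count, its lowest class is also affected. There is no comparator arm in which the same error could offset it.

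**Working it through.** The protocol states no figure to reproduce here. It gives no expected mean, SD or missing share, and Section 8.1 says "the sample size is not based on any inferential statistical considerations".

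**Inputs.** The number of women is from the protocol: "There will be 200 subjects initiated with REKOVELLE® treatment and enrolled", so n = 200. Everything else is assumed: mean μ = 10 oocytes (also 8 and 12), SD σ = 5, and a share m of 2% to 20% of counts missing although the true value is not a documented zero.

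**Mean.** Let the missing women have true mean μₘ. The zero-filled mean differs from the true mean by −m·μₘ, which is never positive. If they resemble the others (μₘ = μ), the reported mean is (1 − m)·μ.

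**SD.** The reported variance is (1 − m)·σ² + m·(1 − m)·μ². It exceeds σ² whenever (1 − m)·μ² > σ², that is, unless the SD is about as large as the mean or larger. So the spread is usually inflated, but not for every possible count.

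For m = 5%: mean = 0.95 × 10 = 9.5; variance = 0.95 × 25 + 0.05 × 0.95 × 100 = 23.75 + 4.75 = 28.5; SD = 5.34. The standard error without missing data is 5/√200 = 0.35, used here only as a yardstick, since the study plans no inference.

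| Missing share m | Women of 200 | Reported mean | Reported SD | Shift in standard errors |
|---|---|---|---|---|
| 2% | 4 | 9.8 | 5.14 | 0.6 |
| 5% | 10 | 9.5 | 5.34 | 1.4 |
| 10% | 20 | 9.0 | 5.61 | 2.8 |
| 20% | 40 | 8.0 | 6.00 | 5.7 |

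With μ = 8, the reported mean is 7.6 at 5% and 7.2 at 10%. With μ = 12, it is 11.4 and 10.8.

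**Lowest response class.** This applies only if the ovarian-response subgroup is built on oocyte count. Let q be the true share in the lowest class. The reported share is q·(1 − m) + m. With an assumed q = 10%, that is 0.10 × 0.95 + 0.05 = 14.5% at 5% missing and 0.10 × 0.90 + 0.10 = 19.0% at 10%.

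**Pregnancy, for comparison.** With an assumed true rate p = 30% and missingness unrelated to outcome, the reported rate is p·(1 − m): 28.5% at 5% missing and 27.0% at 10%. If every missing woman were pregnant, the rate would be p·(1 − m) + m: 33.5% and 37.0%.

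**The case against.** The strongest reply is that few counts will be missing. Oocyte counts arise in the clinic itself, Section 9.2 builds logic checks against missing entries, and Section 4.3 relies on automated queries and expects little loss to follow-up. This stands as a limit on size. It does not answer the withdrawal case, where Section 5.3 closes the record and no query can recover the count. Section 4.3 also concedes that missing data may occur and cause bias.

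Several stronger readings are tempting, but the documents do not support them:

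- **That the rule contradicts Section 8.2.1.** The number missing can be counted before zeros are filled in, so both can be followed. The protocol merely leaves the order unstated.
- **That missing pregnancy outcomes will fall mainly among women already known to be pregnant.** The line "Ultrasound results since last visit, as available" in Section 6.2.3 is a general imaging item. Pregnancy outcome is a separate item there without that qualifier, Section 4.1 requires scans done elsewhere to be obtained, and a telephone interview is allowed. Nothing says how often the scan is done elsewhere.
- **That counting missing outcomes as not pregnant is an error.** Per started cycle, it is a recognised conservative convention.
- **That every outcome is biased.** The rule names pregnancy outcomes and count-type endpoints. It does not name treatment patterns, cancellation, adverse reactions, OHSS or the questionnaire.
- **That embryos transferred should be summarised per transfer.** The choice of all started cycles as denominator is deliberate and separate from missing data.

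**Conclusion.** The point holds for counts. A rule fixed in the protocol treats an unknown oocyte, embryo or blastocyst count as an observed zero, although the data collected allow the two to be told apart. The resulting bias in the means cannot be upward. Its size is the missing share times the mean of the missing women: half an oocyte at 5% missing and one oocyte at 10%, under an assumed mean of 10. The SD is usually inflated. Any effect on the ovarian-response subgroup depends on a definition that the protocol does not give.

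The missing share is unknown and may be small, so these figures show scale and are not a forecast. The endpoints concerned are secondary and descriptive. The overall primary endpoint analysis and the sample size are unaffected; only the primary endpoint's tables by ovarian response could be touched, and only under that same definition. This should be fixed, but it does not undermine the study.

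**What to change.** Reword the sentence in the Protocol Outline so that a count is zero only where the e-CRF documents a non-event: cycle cancelled before pick-up, no oocytes collected, none frozen, or no transfer. Leave every other absent count missing. Report the number observed and the number missing for each count endpoint, as Section 8.2.1 already asks, and put the same rule into Section 8 so that the outline and the body agree.

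The pregnancy rule may stay as the conservative rate per started cycle. Showing the number of missing outcomes and the observed-outcome rate beside it would be a useful but optional addition.

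The cost is a few extra table columns and, for counts, a denominator slightly below all started cycles. Women with documented non-events remain in it at zero. The observed mean then assumes that the missing women resemble the rest. With both numbers shown, a reader can recover the zero-filled mean: for example, 10 × 190/200 = 9.5. No new data are needed, and the change can be made before database lock.
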